## Abstract

**Background:**

Most U.S. K-12 schools have adopted safety tactics and policies like arming teachers and installing metal detectors, to address intentional school gun violence. However, there is minimal research on their effectiveness. Furthermore, sociodemographic factors may influence their implementation. Controlled studies are necessary to investigate their impact on gun violence and related disciplinary outcomes.

**Objective:**

The paper outlines the protocol for a case-control study examining gun violence prevention policies in U.S. K-12 schools. The study aims to investigate if there is an association between the total number and type of specific safety tactics and policies and the occurrence of intentional shootings in K-12 public schools, student disciplinary outcomes, and if urbanicity, economic, and racial factors modify these associations.

**Methods:**

We will create a nationally representative dataset for this study and ascertain a full census of case schools (schools that experienced intentional gunfire on the campus during school hours since 2015) through national school shooting databases. Matched control schools will be randomly selected from U.S. Department of Education’s national database of all public schools. We will analyze 27 school safety strategies organized into seven key exposure groupings.

**Results:**

Supported by the National Institutes for Child Health and Development (R01HD108027-01) and having received Institutional Review Board approval, our study is currently in the data collection phase. Our analytical plan will determine the association between the number and type of school safety tactics and policies with the occurrence of intentional shootings and suspensions and expulsions in a national sample of approximately 650 K-12 public schools. Additional analyses will investigate the effect modification of specific covariates.

**Conclusion:**

As the first national, controlled study, its results will provide novel and needed data on the effectiveness of school safety tactics and policies in preventing intentional shootings at K-12 public schools.

## Introduction

Gun violence is currently the leading cause of death among children and teens in the US [1,2]. Gun violence in K-12 public schools around the US persists as a public health crisis. Over 357,000 students have been exposed to gun violence in K–12 schools since the Columbine High School shooting in Colorado in 1999. These numbers do not fully capture the impact of school shootings on children, teachers, and other school staff who may not have been directly injured by firearms but may have experienced indirect forms of gun violence such as witnessing a shooting. The nature of this kind of violence significantly impacts the well-being of entire school communities, with enormous consequences for children’s health, learning, and development [3,4].

In response to the persistence of this kind of violence, K-12 schools across the US are widely implementing numerous safety tactics and policies as a way to secure their buildings and prepare their communities for the possibility of gunfire on school grounds. However, the effectiveness of these security tactics and policies at deterring school shootings remains largely untested. Implementation of security measures, such as metal detectors, armed school staff, and zero-tolerance policies has significantly changed the daily school experience since Columbine [5]. In 1999, less than 20% of schools had security cameras; now more than 80% do [6]. Similarly, as of 2019, 96% of K-12 schools now conduct lockdown drills, compared with far fewer who implemented such procedures prior to the Sandy Hook school shooting in 2012 [7]. This is significant, as there are currently over 90,000 public K-12 schools across the nation, serving an estimated 51 million children. Unfortunately, there is limited and conflicting evidence surrounding these tactics and policies. Some studies show that more security measures in schools, such as metal detectors and armed guards, can result in students feeling less safe [8–10]. However, other work suggests that students feel safer with these policies [11]. Further, there is evidence that security measures have little effect [12]. Overall, studies evaluating school security policies have been inconclusive and inadequately designed with no comparator or control schools or student populations [13,14].

Thousands of instances of gunfire have occurred in US K–12 schools over the twenty years since the Columbine High School shooting [15]. However, following the Columbine shooting in 1999, the yearly incidence of school shootings remained relatively constant until a noticeable uptick beginning in 2015 [16]. Despite this recent increase, little comparative research has examined what specific safety tactics and policies work to prevent intentional shootings on K-12 school grounds [17]. Definitions of what counts as a “school shooting” currently range from an accidental discharge of a gun at school to injury or death of a student by a firearm. Although the prevention of accidental shootings or suicides are extremely important, our focus in this proposed study is on efforts aimed at the prevention of intentional shootings of other individuals in K-12 public schools, particularly since many existing school safety strategies have been designed specifically to prevent intentional, interpersonal gun violence.

### K-12 school security

In response to the anticipation of school gun violence, millions of K-12 students now walk through airport-style security every day in the US [17]. The effectiveness of such measures is understudied, but some research suggests that visible security measures, such as metal detectors, cameras, and police officers, do not improve school safety or academic achievement and may increase student anxiety and stress [18]. For instance, metal detectors cannot distinguish between different objects made of metal and often require searches by security personnel questioning their effectiveness, while possibly heightening student anxiety [19,20]. Security measures may also exacerbate disparities in school discipline outcomes. Available research on active shooters in schools has been conducted via small sample case-series studies. While limited, this research suggests that commonalities exist across individuals who commit school shootings, such as having experiences with bullying, access to weapons, and poor social skills [21,22]. Research has also illustrated that school shooters are typically teenage, middle-class, White males, that live in suburbs and rural neighborhoods [23] and with parents that own firearms [24].

Despite these known demographics, “hardening” of schools through addition of armed guards, metal detectors, and zero-tolerance policies is more likely to occur in schools that are primarily serving minoritized students and in urban areas of lower socioeconomic status, even after accounting for violent crime rates [3,4,6]. Thus, schools appear to differentially employ security interventions and disciplinary action based on sociodemographic factors unrelated to school safety [25–27]. Critics have argued that this criminalizes students for minor misbehaviors, possibly provoking pathways into the criminal justice system, a phenomenon often described as the school-to-prison pipeline [28–30]. Some patterns of school security usage are associated with increased exposure to crime and violence at school [31,32] and misusage of security may have detrimental effects on academic outcomes [33]. Little research has been completed using readily available data on suspensions and expulsions, as indicators of student criminalization, across disparate school types. In this way, school securitization is part of a broader, poorly understood policy trend to manage, rather than repair, consequences of disinvestment, economic austerity, and unprecedented social inequality. Research on the effectiveness and unintended negative consequences of school safety interventions in a wide variety of communities is critical.

### Prior methodological limitations

Prior studies of school safety tactics and school shootings have been case-series designs, i.e., only involving schools that have experienced shootings. This is a critical methodological shortcoming because there is no way to determine if the safety tactics and policies in question are protective with no comparison group of schools that have not experienced shootings (but that could have) and may have had many of the same safety tactics and policies in place at similar points in time. The present study is therefore employing a population-based, incidence density sampled case-control study of shootings in K–12 schools that includes a national group of schools that have experienced shootings and national comparator group of control schools that have not experienced a shooting.

### Purpose

Using this case-control study design, the study protocol has the following three specific aims and hypotheses,

**Aim 1:** To determine if the total number and specific types of safety tactics and policies are associated with the occurrence of intentional shootings in K-12 public schools.
○ Primary Aim 1 hypothesis—The total number of cumulative safety tactics and policies will be significantly associated with intentional school shootings.○ Secondary Aim 1 hypothesis—When organized into three domains (physical target hardening, emergency response and technologies, and school security), the total number of safety tactics and policies within each domain will be significantly associated with intentional school shootings.**Aim 2:** To determine if the total number and specific types of safety tactics and policies are associated with suspension and expulsion rates in K-12 public schools.
○ Primary Aim 2 hypothesis—The total number of cumulative safety tactics and policies will be significantly associated with student discipline outcomes.○ Secondary Aim 2 hypothesis—When organized into three domains (physical target hardening, emergency response and technologies, and school security), the total number of safety tactics and policies within each domain will be significantly associated with student discipline outcomes.**Aim 3:** To identify if urban/non-urban, economic, and racial disparities modify the relationships between the implementation of safety tactics and policies, suspensions and expulsions, and intentional shootings in K-12 public schools.
○ Aim 3 Hypothesis: Significant urban/non-urban, economic, and racial disparities will modify the relationships between the implementation of safety tactics and policies, suspensions and expulsions, and intentional shootings in K-12 public schools.

## Methodology

### Sampling frame

National data from a random sample of K-12 public schools around the US are being collected for this case-control study. Case schools are being ascertained through a comprehensive review of multiple national school shooting databases, including the K-12 School Shooting database, the Everytown for Gun Safety database on gunfire on school grounds, and the Washington Post database on school shootings, to identify all schools that have experienced an intentional gunfire against others on the campus during school hours. Control schools will be ascertained via random selection from the US department of Education’s national database on all K-12 schools and matched to case schools in 1:1 ratio. The full set of inclusion and exclusion criteria developed by the study team are included [S1 File].

#### Case school ascertainment

We are primarily identifying all school shooting cases via the K-12 School Shooting database (SSDB), as these data detail “all incidents in which a gun is fired, or a bullet hits school property for any reason, regardless of the number of victims, time, day of the week” [34]. Two members of the research team have independently coded this list of incidents to identify the cases that meet the proposed study’s criteria for “intentional school shooting.” And a third member of the study team has reviewed any potential discrepancies in coding efforts. By the study’s completion, the list of cases will be a full, national census of schools that have experienced an intentional shooting on school property, during school hours (including one hour prior to official school activities starting and one hour after all official school activities end) beginning January 1, 2015. The study will exclude accidental discharges and attempted suicides where no other person was targeted or shot. It will also exclude any incidents taking place on a school bus or on school property that is non-contiguous with the school’s primary campus. This list of intentional school shootings meeting the study criteria will be cross-referenced via secondary inspection and inclusion of case data from a series of additional databases that also record and publicly report school shooting incidents, including the Washington Post school shooting incident database and the Everytown for Gun Safety list of gunfire on school ground. These databases are being linked and harmonized to detail all school shooting incidents by the definition above, from January 1, 2015 –December 31, 2023.

#### Control school ascertainment

Control schools are a randomly selected national sample of schools that have not experienced a shooting, by the definition described above and within the same time frame (1/1/2015–12/31/2023). Control schools are being obtained via random selection from a national database of public K-12 schools via the U.S. Department of Education’s National Center for Education Statistics (NCES). For each case school, one control school is being chosen as part of a stratified random sample and matched to each case school based on their geographic state, urban/non-urban status, and elementary/middle/high school status. State and urban/non-urban status will be determined using each school’s address and standard definitions of urbanicity taken from the NCES locale codes.

### Data collection

Driven by preliminary study planning and statistical power calculations, the study protocol intends to collect data on an estimated 658 K–12 public schools (329 cases and 329 controls) across the US.

#### Independent variable—school safety strategies

Data on school safety tactics and policies will be predominantly based on those listed in the School Survey on Crime and Safety (SSOCS); a national survey that is administered via the US Department of Education’s NCES to a representative sample of public schools every two years to assess a range of school safety and security interventions, among other indicators of school violence and school violence prevention. Drawing on this survey and also on the existing literature, our study team has identified a comprehensive set of 27 different school safety tactics and policies, which have been further grouped into seven categories (S2 File). Each school’s safety plan, their student handbook, their code of conduct, their school improvement plan, and/or the school’s facilities information, satellite and Google Street View images, and additional publicly available secondary data sources will be used to identify the specific security tactics and policies in place at both case and control schools during the school year before each pair-matched case school’s shooting event.

It should be noted that public school safety plans are comprehensive documents developed by school leaders that detail preparation and response protocols for a range of possible school situations and emergencies included in the proposed study. Data on school safety strategies are being obtained from each school’s publicly available written school safety plan or handbook online at local school district websites. In the case that a given school’s safety plan is not available online, the research team is emailing the superintendents of the school district directly to inquire if they are able to provide a copy of that specific school’s safety plan for the purposes of this study and in line with the study’s IRB protocol.

Furthermore, in completing the specific aims that address the impact of school safety tactics and policies at different points in time, we are obtaining school safety plans with valid timestamps of the years they went into effect, including the year of a case school shooting. To obtain complete safety information for each school in the study, researchers are triangulating the data obtained via the school safety plans with other reliable and date-stamped sources of data. Using the Google Street View “time machine” feature to obtain images of schools in the index year of each shooting, street-level and satellite imagery data are also being audited to confirm whether external structures of schools have illuminated school entry doors, external barriers, bollards or buffer zones, and/or external security cameras.

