### Data organization and management

#### Study design

The case-control study design is a natural choice in accomplishing the aims proposed here given the relatively rare outcome of school shootings and the need to quantitatively test school safety tactics and policies by including a national comparator group of control schools that have not experienced shootings. In addition, other study designs, such as randomized controlled trials or cohort studies, would be unethical to conduct or would take infeasibly long periods of time to complete, thus underscoring the benefits of utilizing the case-control study design as described here.

Per the study’s Specific Aims, this study is examining associations between safety tactics/policies and various outcomes (Fig 1). As described in Specific Aim 1, our research team is testing relationships between the total number and specific presence of 27 school safety tactics and policies using a case-control design to calculate the odds of intentional school shootings. In Specific Aim 2, we are testing the relationships between the total number and specific presence of 27 types of school safety tactics and policies and the occurrence of school suspensions and expulsions. Aims 1 and 2 are possible due to the temporal specificity of the data, as implementation of safety tactics/policies and occurrence of school shootings and suspensions/expulsions are date stamped.

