#### Data analysis plan and study registration

An estimated 658 K-12 public schools will be included in our study sample. The presence or absence (binary 0–1 variables) of each of the 27 safety tactics and policies in case and control schools before each case school’s shooting will be statistically tested as independent variables of interest. The number of safety tactics and policies that each school has in place (from 0–27) will be statistically tested as independent count variables. And the number of suspensions and expulsions that have occurred will also be statistically tested as a proportion of the number of students in each school. Specific safety tactics and policies found to have small numbers will also be combined into groupings of safety tactics and policies as per prior aggregated categories: external target hardening, internal target hardening, student/staff monitoring, emergency procedures/drills, emergency notification technologies, medical support, and school security staff.

Analyses will begin with descriptive statistics to characterize cases and controls relative to independent variables. Categorical and continuous variables will be explored using frequency distributions, means, medians, standard deviations, skewness coefficients, and ranges. Bivariable analyses of predictor variables for each outcome will consist of t -tests, Chi-squared tests, and nonparametric comparison tests. Collinear independent variables will be identified using Spearman coefficients, tolerance statistics, and condition indices. As this population-based case-control study will be matched on state, urban/non-urban, and elementary/middle/high school status, conditional logistic regression model specifications will be used. The first two aims will adjust for confounders that will be methodologically and theoretically justified. The third aim will include interaction analyses with select effect modifiers: urban/nonurban, economic, and racial disparities. Despite having matched on these variables, effect modification analyses with these variables are possible and commonly conducted in case-control studies. Disparities analyses will include adjustments for sparse data. Researchers will reasonably limit the final group of predictor variables to promote statistical efficiency and provide the best unbiased estimators.

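### External safety features are audited on images from the year of the shooting, although exposure is defined as the school year before it, so hardening added after a shooting can be coded as prior exposure, mainly in case schools

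*Protocol article*

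**What the plan says.** All of this is in the protocol article.

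- **Exposure window.** Under *Independent variable—school safety strategies*, documents and satellite and Street View images are to identify the tactics "in place at both case and control schools during the school year before each pair-matched case" school's shooting. *Data analysis plan and study registration* agrees: the variables tested are the "safety tactics and policies in case and control schools before each case" school's shooting.
- **Images.** Later in the same *Independent variable* section, the Street View archive is used as a "feature to obtain images of schools in the index year of each shooting". The images are audited to confirm "illuminated school entry doors, external barriers, bollards or buffer zones, and/or external security cameras".
- **Safety plans.** That section also says the team collects "school safety plans with valid timestamps of the years they went into effect, including the year of a case school shooting".
- **Date stamps.** *Study design* says Aims 1 and 2 are possible because "implementation of safety tactics/policies and occurrence of school shootings and suspensions/expulsions are date stamped". Nowhere does the article say that a source dated after the shooting is set aside.
- **Controls.** *Control school ascertainment* requires that a control had no qualifying shooting in 2015–2023.

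**The concern.** The year of a shooting is not the school year before it, and part of that year falls after the event. If the year is a calendar year and the shooting is in January, nearly all of it does. An image from the index year may therefore show what the school did because of the shooting. The article's *Discussion* itself says that gun violence has led schools to adopt safety measures, so a reaction by a school that has just had a shooting is plausible.

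The matched control is imaged for the same index year but has had no event of its own. The resulting misclassification differs between cases and controls, and it has a direction: features look more common in cases than they were beforehand. A protective feature can then look null, and a null feature harmful. Matching, covariate adjustment, targeted maximum likelihood and multiple imputation do not correct an exposure that is measured after the outcome. At stake are the items read from images, the external target hardening group and, to a lesser degree, the cumulative count used for the primary Aim 1 hypothesis.

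**Working it through.** **Step 1: the texts side by side.** The definition requires the prior school year. The analysis plan requires a time before the shooting. The image rule takes the index year and gives no cut-off within it. An image taken in the index year after the shooting satisfies the image rule and fails the other two.

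**Step 2: inputs.** From the article: 329 cases and 329 controls, matched 1:1 (329 + 329 = 658, as stated); 27 tactics; external features audited from images, counted here as four. Not in the article, so assumed:
- p, the true prevalence of a feature before the shooting, equal in cases and controls (true odds ratio 1);
- f, the share of case-school images that postdate the shooting;
- a, the share of case schools without the feature that add it afterwards and before the image;
- a standard deviation of 4 for the count.

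**Step 3: one feature.** Observed prevalence in cases is p′ = p + (1 − p)·f·a. The apparent odds ratio is [p′/(1 − p′)] ÷ [p/(1 − p)].

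| p | f | a | p′ | Apparent OR |
|---|---|---|---|---|
| 0.30 | 0.50 | 0.20 | 0.37 | 1.37 |
| 0.50 | 0.50 | 0.20 | 0.55 | 1.22 |
| 0.30 | 0.50 | 0.40 | 0.44 | 1.83 |
| 0.50 | 0.50 | 0.40 | 0.60 | 1.50 |
| 0.20 | 0.25 | 0.10 | 0.22 | 1.13 |
| 0.50 | 0.25 | 0.10 | 0.5125 | 1.05 |
| 0.80 | 0.25 | 0.10 | 0.805 | 1.03 |

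For the first row, (0.37/0.63) ÷ (0.30/0.70) = 0.587 ÷ 0.429 = 1.37. With f = 0 the odds ratio is 1 in every row.

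A protective feature is affected in the same way. With a true odds ratio of 0.7 and control prevalence 0.50, the true case prevalence is 0.7/1.7 = 0.412. With f = 0.5 and a = 0.2 it is observed as 0.412 + 0.588 × 0.10 = 0.471, an apparent odds ratio of 0.89.

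**Step 4: the 0–27 count.** The mean shift in cases from the imaged items alone is 4·(1 − p)·f·a. With no allowance for within-pair correlation, the standard error of the case–control difference is 4·√(2/329) = 0.312. With f = 0.5 and a two-sided 5% test:

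| p | a | Shift (tactics) | z | Chance of rejecting a true null |
|---|---|---|---|---|
| 0.50 | 0.20 | 0.20 | 0.64 | 10% |
| 0.30 | 0.20 | 0.28 | 0.90 | 15% |
| 0.50 | 0.40 | 0.40 | 1.28 | 25% |
| 0.30 | 0.40 | 0.56 | 1.80 | 43% |

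At the mild end (f = 0.25, a = 0.10, p = 0.50) the shift is 0.05 tactic and the rejection rate stays at about 5%.

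**The case against.** The strongest reply is that the governing definition is already right. It is stated twice, it expressly covers the images, and the image sentence may only describe loosely how sources are obtained. The article does not define the index year; if it means the prior school year, the conflict disappears. The images also serve to confirm and triangulate dated documents and need not settle an item alone. This lowers the certainty that post-event features will in fact be coded, but it does not remove the conflict. The plain meaning of the image sentence is the year of the shooting, and an auditor who follows it has no instruction to reject a later image.

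A reader might infer three stronger things that the article does not support.

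- *That shooting-year safety plans are coded as exposure.* The article says only that the shooting year is included among the years collected. Stamps showing the year of effect are what would let the team select the prior-year version. What stands is that a year-level stamp cannot separate before from after within the shooting year.
- *That the error occurs in cases only.* Controls can also add features during the index year, through secular trend or in reaction to an event nearby. The extra reaction to a school's own shooting is what is specific to cases, so the error is mainly, not only, in cases.
- *That the primary count is severely biased.* The image rule reaches about four of 27 tactics. False-positive rates much above those in Step 4 would need widespread contamination through the plans, which is the part the text supports least.

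**Conclusion.** The concern holds in a limited form. The image rule conflicts with the study's own exposure definition and, as written, allows reverse causation in the imaged external features and the external target hardening group. The direction is upward, provided that case schools react to their own shooting by adding features more than controls do. The size is unknown, because prevalence, image timing, adoption after a shooting and the spread of the count are all assumed. Under the central assumptions (half of images after the event, 20% adding a feature) the item odds ratio is inflated to 1.22–1.37 and the count has a false-positive rate of about 10–15% instead of 5%. Under mild assumptions both are close to nominal. Safety plans are a secondary point about the resolution of dates.

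**What to change.** Reconcile the image sentence with the exposure definition by setting one cut-off for both members of a pair, namely the case school's shooting date.

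1. Count a tactic as present only from an image, plan or document dated before that date: the prior school year, or for images the most recent capture before the shooting.
2. For plans stamped only by year, use the version in effect in the prior school year.
3. Record the capture or effective date of each source, and code the item as missing where no pre-shooting source exists.
4. Run a sensitivity analysis restricted to prior-school-year sources.

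The cost is a wording change in the protocol and codebook, plus a re-check of dates on images already audited. Some external items will become missing or rest on older images. Data collection is under way, so the change is cheaper now than after coding is complete.
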